# Trial Protocol

## Participants

A random sample of 460 African American youth in 5th grade and their primary caregivers will be recruited for the proposed study. Families will be sampled from 8 Georgia counties. We selected nonmetropolitan counties (population density <100 persons per square mile) with large proportions of African American residents (>25%) that represent the range of non-urban environments in the South in which African American live . These areas are demographically and economically similar to those in which SAAF and SAAF–T were originally tested. Table 1 presents county demographic characteristics. In past trials, we examined the possibility that county heterogeneity in these indicators affected intervention response: no effects were detected 

| Table 1. Demographic characteristics of the counties to be included in the sample (AA = African American) |        |               |                               |            |
|-----------------------------------------------------------------------------------------------------------|--------|---------------|-------------------------------|------------|
| County                                                                                                    | AA (%) | Single Parent | Median AA Family Income (\$k) | AA <HS (%) |
| Baldwin                                                                                                   | 43     | 48            | 26.2                          | 38         |
| Burke                                                                                                     | 50     | 51            | 17                            | 45         |
| Emanuel                                                                                                   | 32     | 50            | 15.6                          | 47         |
| Green                                                                                                     | 38     | 50            | 21.4                          | 46         |
| Laurens                                                                                                   | 35     | 49            | 20.0                          | 43         |
| MacDuffie                                                                                                 | 38     | 50            | 20.1                          | 50         |
| Screven                                                                                                   | 43     | 44            | 24.9                          | 47         |
| Warren                                                                                                    | 56     | 50            | 19.7                          | 56         |

Using data from the Department of Education , we estimated a pool of no less than 800 eligible households from which to sample 460 families (54.5%). Based on recruitment rates in our prior prevention trials (65%-90% of eligible household), an ample number of families will be available for us to reach our sampling goals.

## Methodological Overview.

Figure 4 presents an overview of the study design.

[figure not shown]

### Sampling frame and eligibility.

Consistent with our prior prevention research protocols, youth and their primary caregivers will be recruited in random order from lists of students in public schools in the targeted counties. Very few (<2%) rural African American youth in these areas attend private schools; thus, lists of public-school students approximate a population frame. Eligibility criteria for youth include age of 10-11 years and identification by the family and school as African American. Primary caregivers are not required to identify as African American. Because we are not currently working with families of early adolescents in the areas listed in Table 1, few families will already be taking part in one of our projects. In the unlikely event that a family is already participating in a CFR project, that family will be ineligible for recruitment. Siblings and stepsiblings who both are in the 5th grade will be excluded, because the inclusion of more than one participant from the same family introduces confounds that make interpretation difficult.

### Random assignment and contamination.

After pretest, families will be assigned randomly to one of four experimental groups: (a) *preadolescent inoculation*, (b) *mid-adolescent inoculation*, (c) *dual inoculation* control, and (d) control. Although the efficacy of SAAF and SAAF–Teen have been established, inclusion of a

control condition provides a baseline from which to compare normative alcohol use behavior in the population to both single- and dual-inoculation groups; it is also essential for comparing the single inoculations' economic efficiency. Preadolescent inoculation families will be assigned to receive SAAF at age 11 with no further intervention. Mid-adolescent inoculation families will receive SAAF–Teen at age 14. The dual-inoculation group will be assigned to receive both SAAF at age 11 and SAAF–Teen at age 14. The control condition involves no intervention contact. Participants will be notified if they are selected to participate in SAAF shortly after pretest. No participants will know if they are to receive SAAF–Teen until several months prior to its implementation. For each intervention implementation, families who are not attending a program receive written information by mail regarding adolescent development and alcohol use. Sending these materials is intended to maintain investment in the project for families who are not attending an intervention. No alcohol use effects are expected based on receiving written materials. All families will be followed across the course of the proposed study and assessed regardless of the number of intervention sessions they attend (intent-to-treat design). Information will be collected from family members about their participation in family enrichment programs offered in the school or community. The potential effects of participation in other programs (contamination) will be examined and statistically controlled in data analyses, as Lang et al. described.

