## **Data Analysis**

### **Data management, exploratory data analysis, psychometrics, and experimental considerations.**

Data will be organized and cleaned following quality control procedures that involve analyses of outliers and unexpected or inappropriate missing-data patterns. Next, items' distributions and constructs' psychometric properties will be examined. We will establish equivalence among experimental conditions with ANOVAs and chi-square tests on baseline levels of alcohol use, preadolescent protective processes, and demographic variables. Any departures from equivalence will be controlled in subsequent analyses. All primary analyses will be intent-to-treat.

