#### **Aim 1.**

Mean differences in alcohol use by experimental group at wave 5 (~10 months after SAAF-T implementation) will be tested with structural equation models (SEM) as presented in Figure 6. These models are roughly equivalent to ANCOVA, but the SEM software permits FIML-based estimation of parameters as well as options for forming latent alcohol use constructs and greater precision in specifying and testing model parameters. We will investigate main effects on onset, frequency of use, binge use, and alcohol use problems as well as aggregate alcohol risk indices validated in prior trials to establish mean differences in use as a

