### Aim 2.

This aim examines pathways through which different inoculation strategies affect distal (W5) alcohol use. Analyses in

Aim 1 serve as a baseline for examining mediation and the subsequent decomposition of intermediate effects. SEM provides a parsimonious tool

Figure 7. General model for SEM of intervening processes

[figure not shown]

that enables the analyst to identify indirect pathways of influence between intervention assignment and high school alcohol use outcomes. The potential mediators include SAAF-targeted protective processes, SAAF–Teen-targeted protective processes, and preadolescent (Wave 3) alcohol use. Figure 7 provides a general specification for intervening variable models. Baseline or pretest levels of distal and proximal processes will be controlled in all analyses. For example, in analyses of SAAF–T intervention-targeted processes as a mediator, pretest (Wave 4) levels of these processes will be controlled when testing for posttest (Wave 5) changes. Because multiple protective processes are targeted in each program, we will approach their operationalization with diverse methods. First, we will create scores that index the number of protective processes that a youth or family evinces using established cutoff scores. Such indices account for the numbers of protective factors present rather than variability in any particular factor. We have used this approach previously, and it is sensitive to intervention effects. We have also had success in forming latent constructs from sets of interrelated intervention-targeted mediators. In these analyses, we will confirm the protective processes’ underlying dimensionality and examine invariance in the protective factors’ measurement model across time. We will test uncorrelated protective processes in separate models. Significance of mediational effect tests will be assessed with bootstrapping methods per MacKinnon.

Statistical power. With Monte Carlo simulation ( $n = 100$  per group), we evaluated power to detect the significance of path coefficients that vary in their “true” magnitude, holding the other parameters in the model constant at values estimated from previous research. For the paths included in Aim 2, power ranged from .7 to .9 for detecting path coefficients ranging from .2 to .4 ( $p < .05$ ). This suggests that we will have the power to detect small and medium effect sizes among model paths.

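### Controlling for outside programme participation after randomisation can bias the Aim 1 intent-to-treat contrasts, and baseline covariates should be fixed in advance, not chosen by equivalence tests

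*Combined protocol and SAP*

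**What the plan says.** Three statements bear on which covariates enter the Aim 1 models.

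- **Contamination (Random assignment and contamination).** "Information will be collected from family members about their participation in family enrichment programs offered in the school or community". Then: "The potential effects of participation in other programs (contamination) will be examined and statistically controlled in data analyses". The method is referred to a cited paper on cross-contamination in a sexual risk reduction trial and is not described. No timing is given for the measurement, and no analysis is exempted. The same section fixes when assignment happens: "After pretest, families will be assigned randomly to one of four experimental groups".
- **Baseline covariates (Data Analysis, the subsection on data management and experimental considerations).** "We will establish equivalence among experimental conditions with ANOVAs and chi-square tests on baseline levels of alcohol use, preadolescent protective processes, and demographic variables". Then: "Any departures from equivalence will be controlled in subsequent analyses". No threshold, number of tests or fixed list is given.
- **Principle (same subsection).** "All primary analyses will be intent-to-treat".

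Aim 1 says of its models, "These models are roughly equivalent to ANCOVA", and refers to Figure 6, which is not shown in the text available. Aim 2 has a general rule: "Baseline or pretest levels of distal and proximal processes will be controlled in all analyses". Aim 3 takes its outcome effects from the Aim 1 intent-to-treat analyses.

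**The concern.** Outside programme use during follow-up happens after assignment and may respond to it. Families know early whether they will receive SAAF. All have agreed to attend if selected, and control families are then offered no programme. They may look elsewhere; programme families may be drawn towards other offerings or away from them. Engaged families may also be both likelier to attend and less likely to have a child who drinks. A model that holds such a variable constant does not in general estimate the effect of assignment: it removes any part of the effect that runs through participation, and it conditions on a variable that shares causes with the outcome.

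The baseline rule is a different and milder problem. Under sound randomisation, an equivalence test can flag only chance differences. The covariate set is then unknown until the data are seen, and a prognostic variable that happens to be balanced is left out, although adjusting for it would have narrowed the interval.

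At stake are the primary Aim 1 contrasts, and through them the cost-effectiveness results of Aim 3.

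**Working it through.** **The plan's own figures.** Neither rule has a figure attached. The only Aim 1 design figure is in the Power section: effects of .13 and .15 at power .80 and .90, with 100-115 families per group. Reading the effect as Cohen's f, with one numerator degree of freedom, N = 460 and two-sided .05, the noncentral F gives .795 and .894, so the statement reproduces. It is not in dispute here. The calculations below use 100 per arm, in line with the 400 expected completers (87% of 460).

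**1. Contamination rule.** In a linear model the link between the two contrasts is exact algebra:

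adjusted contrast − unadjusted contrast = −(p1 − p0) × b

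Here p1 and p0 are the proportions of treated and control families using other programmes, and b is the participation coefficient in the adjusted model. It reflects both any effect of those programmes and any shared causes. The unadjusted contrast is the intent-to-treat effect. The shift is therefore zero if participation is equal across arms, or if b is zero.

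The documents give none of p1, p0 or b. Assumed for illustration: engagement raises participation by 1 log-odds per SD and lowers alcohol use by .4 SD; other programmes lower use by .2 SD; the direct effect of assignment is −.30 SD. In simulations of 2 million families, b comes out at about −.54.

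| Control v treated participation | Intent-to-treat effect | Adjusted | Shift |
|---|---|---|---|
| 33% v 15% | −.26 | −.36 | −.10 |
| 33% v 57% | −.35 | −.22 | +.13 |
| 33% v 28% | −.29 | −.32 | −.03 |
| 33% v 38% | −.31 | −.28 | +.03 |
| 10% v 5% | −.29 | −.32 | −.03 |
| 33% v 33% | −.30 | −.30 | 0 |

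Check by the formula: .18 × .54 = .10; .24 × .54 = .13; .05 × .54 = .03.

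With no effect of assignment or of other programmes, and only the shared cause left, the adjusted contrast is −.06 (33% v 15%) or +.08 (33% v 57%) where the truth is zero. With neither the shared cause nor a programme effect, 33% v 15% gives −.30 both ways.

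A second set of simulations used different assumptions: 100 per arm, 25% participation for an average control family, 4,000 replicates.

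- Null shifts were −.04 SD (odds ratio of participation, treated v control, about 0.5), −.06 (about 0.25) and +.05 (about 2).
- With a stronger shared cause and an odds ratio of about 0.25, the shift was −.13 and the type I error 16%. As a check, the standard error of a pairwise contrast is √(2/100) = .141, so .134 is .95 standard errors, and Φ(−1.01) + Φ(−2.91) = .16.
- Without the participation covariate, null rejection was .044 to .054.

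**2. Baseline rule.** The chance of at least one flagged variable under sound randomisation is 1 − .95^k, assuming k independent tests at .05 (the plan states neither the number nor the threshold):

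| k | 5 | 10 | 15 | 20 | 25 |
|---|---|---|---|---|---|
| Chance | 23% | 40% | 54% | 64% | 72% |

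Correlated baseline variables would change these figures.

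The effect on the contrast was simulated with four arms of 100 and 12 baseline covariates. Selection by test gave a mean of 0.00 under the null and 0.30 for a true 0.30, with type I error .046 to .051, so there is no bias. Power for a 0.30 SD contrast was:

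- one covariate correlated .5 with outcome and eleven at .1: .57 with selection, .73 with all prespecified;
- all twelve at .1: .57 with selection, .61 with all prespecified.

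Check on the first line: the covariates explain .25 + 11 × .01 = .36 of the variance, so the standard error falls from .141 to .141 × √.64 = .113. Normal power is then Φ(.30/.113 − 1.966) = .75, before the cost of estimating 12 coefficients.

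**The case against.** The strongest reply is that the plan never says participation will be a covariate in the primary Aim 1 model. The method is left to a cited paper, the Aim 1 section names no such covariate, and primary analyses are declared intent-to-treat. The protocol also ties that term to following every family whatever its attendance, which covariate adjustment does not breach. This stands in part: a reader might infer that the plan commits itself to abandoning intent-to-treat, and the text does not go that far. But the sentence covers data analyses without exception, so an analyst could follow it in Aim 1 without departing from the plan. The ambiguity itself needs removing.

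A second reply is that the bias needs arm differences and causal links that the documents do not report, and that with gaps of five points the shift is only about .03 SD. That is right. A reader might take the larger illustrations as estimates, such as the −.10 shift on an effect of −.26; they are not. Unequal participation alone is not enough either: the shift also vanishes if participation is unrelated to alcohol use given arm.

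Third, a reader might infer that testing for baseline equivalence also biases the contrasts, or that baseline alcohol use goes unadjusted. The simulations do not support the first. The second cannot be asserted: Figure 6 is not shown and may fix a baseline covariate, and Aim 2 has its own pretest rule. A covariate fixed there would shrink the precision loss but would not remove the rule on departures.

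**Conclusion.** The concern holds in a limited form. As written, the contamination rule permits adjustment for a post-randomisation variable in the primary analysis. That can bias the Aim 1 contrasts in either direction and carry into Aim 3. The size cannot be known from the documents; the illustrations run from about .03 to .13 SD, or about 0.2 to 0.9 of the .141 standard error of a pairwise contrast at 100 per arm. They rest on assumed participation rates, an assumed shared cause and, in some scenarios, an assumed programme effect, in a linear model. If assignment leaves outside participation unchanged, that model has no bias.

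The baseline rule is a matter of prespecification and precision, not of bias. The loss depends on how prognostic the omitted covariates are. The .57 against .73 comparison assumes one covariate correlated .5 with the outcome; if few youths drink at baseline, alcohol use at Wave 1 may predict less than that, and .57 against .61 is the more cautious comparison.

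**What to change.** 1. In Random assignment and contamination, and again under Aim 1, state that participation in other programmes after randomisation is not a covariate in the primary Aim 1 models. Report it by arm, and use it only in a sensitivity analysis labelled as such and described in the plan itself.
2. Replace the rule on departures from equivalence with a fixed list of baseline covariates that the documents show are available: Wave 1 alcohol use, county, household income and caregiver education. Add pre-randomisation programme participation only if it is collected at Wave 1. The Measures section does not list it at any wave, so this must be confirmed first.
3. Present the baseline table descriptively, without tests.
4. State that Aim 3 uses the contrasts from these primary models.

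This changes wording only and needs no new data. The cost is a few degrees of freedom: with eight counties, 7 indicators plus one term each for the other three variables makes 10 coefficients, against about 400 completers.

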### **Repeated assessments and attrition.**

Families will participate in 5 annual assessments. Wave 1, the baseline assessment will occur when youth are age 11 and approximately 3 months prior to implementation of SAAF. Wave 4 will occur just prior to the implementation of the SAAF–Teen. The final assessment, Wave 5, occurs approximately 10 months after implementation of SAAF—Teen. In previous

basic research and prevention trials

conducted at CFR, 5-year retention

rates ranged from 88% to 92% .

We plan conservatively for a 13%

attrition rate, ensuring that 400

[figure not shown]

participants (87% of 460) will complete the trial. Figure 5 presents the project timeline.

## Family Recruitment and Retention

The recruitment procedures will be similar to protocols used in our previous prevention trials with rural African American families. These protocols rely on community liaisons (CLs), residents of the counties from which families are sampled; they serve as contacts between CFR and the communities. They are selected on the basis of their positive reputations and extensive social contacts in their communities. The CLs work with the recruitment coordinator to enroll families, then remain in contact with participating families and track changes in the addresses and phone numbers of families who move.

**Family recruitment will be conducted as follows:**

(a) Sampling lists. As in the investigators' past and ongoing studies, research staff work with school staff to identify eligible youth and develop a list from which to sample. We have excellent relationships with schools in the counties listed in Table 1 (see Section 14 for support letters from school officials).

(b) Introductory letter. Caregivers of African American youth receive a letter introducing CFR, emphasizing its focus on health and resilience in African American communities, and informing caregivers that researchers are interested in screening families in the community for participation in a research project. Families are advised to expect a phone call from a local

representative (the CL).

(c) Phone screening. CLs follow up letters with phone screenings to primary caregivers to determine potential eligibility. CLs call families from participant lists in random order to ensure diverse representation of available families. If a family is potentially eligible, a screening/enrollment home visit is scheduled.

(d) Home visit. At the home visits, CLs confirm eligibility, describe the project in detail, and answer any questions the family members may have. Family members are informed that all project participants are expected to participate in annual data collection home visits over the next 5 years. In addition to these home visits, some families, selected by “chance,” will be asked to participate in a prevention program when their youth enter 6th grade, a similar program 3 years later, or both programs. Families must agree to attend if they are selected for either of the programs. If parents and youth agree, a pretest assessment visit is scheduled. Informed consent/assent is obtained at pretest.

#### **Monetary incentives.**

At each data collection, parents will receive \$80 and target youth will receive \$20. Focus group feedback from rural African Americans indicated that these amounts are appropriate compensation for a 1–2-hour data collection visit and acknowledge that the researchers consider their time to be valuable. We explicitly explored in focus groups and post-data-collection debriefings the potential for this level of financial incentive to be overtly coercive for families who are economically distressed. Neither community members nor the UGA IRB consider this level of compensation to be coercive.

